## Abstract

Irritable bowel syndrome (IBS) is a functional gastrointestinal disease in the pathogenesis of which gut dysbiosis may play an important role. Thus, probiotics, prebiotics, or microbiota metabolites, such as butyric acid, are considered to be effective therapy for IBS. However, there are still no trials presenting the efficacy of these three biotic components administered simultaneously. This study aims to evaluate the effects of the product comprising sodium butyrate, probiotics, and short-chain fructooligosaccharides (scFOS) on the severity of clinical IBS symptoms and the quality of life (IBS-QOL). This is a randomized double-blind placebo-controlled trial conducted in 120 adults with IBS diagnosed according to Rome IV criteria. The intervention group (n = 60) will receive a mixture of the following components: 300 mg of colon-targeted microencapsulated sodium butyrate combined with probiotic *Lactobacillus* strains (*L. rhamnosus* and *L. acidophilus*) and *Bifidobacterium* strains (*B. longum*, *B. bifidum*, *B. lactis*), and 64 mg of prebiotic scFOS. The control group (n = 60) will receive a placebo (maltodextrin). The primary outcomes will be changes in IBS symptoms with the use of the IBS-Severity Scoring System (IBS-SSS), IBS-Global Improvement Scale (IBS-GIS), IBS-Adequate Relief (IBS-AR), and IBS-QOL after 12 weeks of intervention. The secondary outcomes will be the type of stools, patient-recorded symptoms, adverse events, anthropometric and nutritional parameters, and inflammatory cytokine levels. The findings will provide the first evidence of the use of a combination of three biotic compounds in IBS. The study was registered in the clinicaltrials.gov registry under the number NCT05013060.

## 1. Introduction

Irritable bowel syndrome (IBS) is one of the most common functional gastrointestinal disorders characterized by recurrent abdominal pain and altered bowel habits in the absence of an organic disease [1]. The prevalence of IBS ranges from <5% up to 20% depending on the countries or regions and the criteria used [2,3,4]. Depending on the predominant alteration in bowel habits, IBS can be classified into diarrhea-predominant IBS (IBS-D), constipation-predominant IBS (IBS-C), and IBS with mixed bowel habits (IBS-M) [1]. Patients who meet diagnostic criteria for IBS, but whose bowel habits cannot be categorized into one of the three groups should be classified as having unclassified IBS [1].

The pathogenesis of IBS is multifactorial with no single etiology but with a wide spectrum of abnormalities including motility disturbances, visceral sensitivity, altered mucosal immune functions, increased intestinal permeability, disturbances in gut microbiota composition, or altered sensory neuron activation and central nervous system processing [1,5,6,7]. It is currently assumed that gut microbiota dysbiosis may be a potential trigger of IBS inducing most of the pathological conditions described above [6,7,8,9]. Gut microbiota dysbiosis is defined as an imbalance of gut microbial communities and their functional activities within the intestines, which is often associated with disease [10]. Recent research suggests that the gut microbiota is involved in many functions of the human body: it affects nutrient digestion and absorption; it is responsible for immune system function, especially the non-specific immunity provided by the gut-associated immune tissue (GALT), and anti-inflammatory and regulatory activity of GALT; it shapes the intestinal epithelial barrier; affects the microbiota–gut–brain axis [11].

There is evidence of significant alterations in the gut microbiota composition in IBS patients [12,13,14]. Analyses of fecal samples showed decreased proportions of the genera *Bifidobacterium* and *Lactobacillus* and increased ratios of the phylum *Firmicutes*: *Bacteroidetes* in most studies. A recent meta-analysis of microbiome studies found significantly lower abundances of *Lactobacillus*, *Bifidobacterium*, and *Faecalibacterium prausnitzi*, one of the main butyrate producers in the intestine, in IBS patients compared with healthy controls [14]. Moreover, a reduction in butyrate-producing bacteria in patients with IBS-D and IBS-M was found in another study [15]. Butyrate together with acetate and propionate are short-chain fatty acids (SCFAs) with biological effects on the gastrointestinal ecosystem [16]. Butyrate constitutes a key source of energy for enterocytes and has a trophic effect on the colon epithelium, supporting the restoration of the disrupted structural and functional integrity of the epithelial barrier [17]. Butyrate may also affect the composition of intestinal microbiota by inhibiting the proliferation of pathogens and fostering desirable strains [18]. Moreover, butyrate beneficially affects several inflammatory cytokines and myeloperoxidase activity via inhibition of nuclear factor kappa B [19]. These unique properties of butyrate are believed to result in several beneficial effects impacting gut functionality. Given that patients with IBS may suffer from low intestinal butyrate concentrations, as mentioned above, a targeted supplementation to distal parts of the intestine using microencapsulated butyrate has been hypothesized to benefit patients with IBS. In fact, a recent study in IBS patients supplemented with microencapsulated sodium butyrate at a dose of 300 mg per day for 12 weeks found a decrease in the frequency of both abdominal pain and the feeling of incomplete evacuation [20].

Another approach to increase intestinal SCFA concentrations (including butyrate) is the administration of probiotics, prebiotics, or synbiotics (probiotics combined with prebiotics). All of them have the potential to modify intestinal dysbiosis and increase intestinal SCFA production [21], thus bringing therapeutic benefits to IBS patients [22,23,24]. Probiotics are live microorganisms that, when administered at the right dose, have a positive effect on human health [25]. Prebiotics (most often oligosaccharides such as fructooligosaccharides (FOS) or galactooligosaccharides) are substrates that are selectively utilized by host microorganisms conferring a health benefit [26]. There are clinical studies showing the effect of probiotics, prebiotics, and synbiotics in patients with IBS [22,23]. Recently, we reported that a multi-strain synbiotic preparation containing probiotic *Lactobacillus* and *Bifidobacterium* strains and prebiotic short-chain FOS (scFOS) was associated with a significant improvement of IBS-D symptoms and was safe and well-tolerated [27]. These results suggested that the use of this synbiotic offers a benefit for IBS-D patients. However, there are no studies demonstrating the efficacy of a mixture of colon-targeted butyrate and probiotics or synbiotics. Thus, the current study aims to assess the efficacy of colon-targeted microencapsulated sodium butyrate combined with the synbiotic preparation we studied previously in IBS patients.

## 2. Experimental Design

### 2.1. Aim and Hypothesis

The main goal of the study is to assess the effects of the product comprising microencapsulated sodium butyrate and the probiotic mixture of two *Lactobacillus* strains (*L. rhamnosus* and *L. acidophilus*) and three *Bifidobacterium* strains (*B. longum*, *B. bifidum*, and *B. lactis*) and small amounts of prebiotic scFOS on the incidence and severity of clinical symptoms in patients diagnosed with IBS based on the Rome IV criteria. The primary hypothesis is that this mixture supplementation will reduce IBS symptoms and improve the patient’s quality of life.

### 2.2. Study Design

This study will be a prospective, randomized, double-blind controlled trial. One hundred twenty patients from the outpatient clinic at the Gastroenterology Department of the Medical University of Lodz (Poland) will be enrolled in the study. The intervention group (n = 60) will receive the study product containing a mixture of microencapsulated butyric acid, probiotic *Lactobacillus* and *Bifidobacterium* strains, and prebiotic scFOS. The control group will receive a placebo—maltodextrin. The duration of the intervention will be 12 weeks. The study schedule will include five visits: the screening visit, whose purpose is to qualify patients to be enrolled in the study, the baseline visit after up to two weeks after the screening visit, at which participants will be randomized either to the intervention or placebo group, and three follow-up visits (after a 1-week run-in period) at weeks 4, 8, and 12 ± 3 days after the start of the intervention. The visit after eight weeks of intervention will be a phone visit by a researcher, the remaining visits will take place at the clinic. The study protocol diagram is presented in Figure 1.

Once recruited, the participants will receive a diary to fill out on a daily basis. Participants will also be monitored by interviewers via phone every week of the study. The study products will be provided to participants at the baseline visit and at the week 4 visit. At the baseline visit, the participant will be asked not to take the product during the first week (a 7-day run-in period) and to make daily patient-diary entries (containing information about the number and type of stool and the severity of specific IBS symptoms); on the seventh day, a telephone interviewer will instruct each participant to take the study product from the next day onwards.

The patients will be informed of the purposes and conditions of this study and will be asked to sign the relevant informed consent form. The patients will also be informed of the option to refuse and withdraw their consent at any time, without stating the reason or suffering any consequences, and without losing the right to receive further care at the Gastroenterology Department or the outpatient clinic. The patients will receive no compensation for their participation in the study. The study protocol was approved by the Ethics Committee at the Medical University of Lodz, Poland (approval number RNN/213/20/KE). The trial will be conducted in accordance with the ethical principles set out in the Declaration of Helsinki and the guideline on Good Clinical Practice. The study was registered in the clinicaltrials.gov registry (ClinicalTrials.gov identifier: NCT05013060).

### 2.3. Randomization

The subjects will be randomly assigned to study groups (receiving butyrate sodium + probiotics + scFOS or placebo) according to a computer-generated randomization list. In order to ensure a balance in the sample size across groups over time, a block randomization model will be applied, with a block size of 4 [28]. The block size will not be disclosed to the investigators, and both the investigators and the patients will be blinded to group allocation.

### 2.4. Intervention

Study participants will receive a preparation of colon-targeted microencapsulated sodium-butyrate, probiotics, and small amounts of scFOS (Actilight^®^, Beghin Meiji, Marckolsheim, France) or placebo supplied by Biocare Copenhagen, an affiliate of DSM Nutritional Products Ltd. (Table 1).

Microencapsulated sodium butyrate is a colon-release preparation containing a pH-dependent polymer, anionic methacrylate copolymer, E 1207 (EmergoPharm Sp. z o.o. Sp.K., Konstancin-Jeziorna, Poland), which had been recently validated for targeted colon delivery [29]. The dosage forms are hard gelatin capsules (Lonza, Bornem, Belgium), with the placebo capsules containing maltodextrin. All capsules will be identical in size, color, texture, and taste and will be marked as product A or B. The packaging of both products will look identical and will have an inscription containing the title of the study, the approval number of the Ethics Committee, and the expiry date.

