### 4.10. Statistical Analyses

#### 4.10.1. Sample Size Calculation

Based on the effects observed in the previous study, in which we used a similar probiotic and prebiotic combination, but without microencapsulated sodium butyrate, in IBS patients [27], we have estimated that a sample size of 35 participants per group would be required to reach clinical significance. With an estimated drop-out ratio of about 20%, the total sample size would need to be 80 participants, which would ensure 80% power to demonstrate significance with a *p*-value < 0.05. To further enhance the statistical power, the sample size was ultimately set to 60 participants/cases per group, with a total of 120 patients to be included in the study.

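### One product letter per arm, allocated in fixed blocks of 4 at one clinic: learning one patient's treatment decodes both letters, and withholding the block size does not prevent that

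*Protocol article*

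**What the plan says.** **Marking (protocol article, 2.4 Intervention).** "All capsules will be identical in size, color, texture, and taste and will be marked as product A or B". The packaging of the two products is described as looking alike and "will have an inscription containing the title of the study, the approval number of the Ethics Committee, and the expiry date". The article lists no patient or kit number there, and no letter on the pack either.

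**Allocation (2.3 Randomization).** A computer-generated list is used: "a block randomization model will be applied, with a block size of 4". The stated protection is: "The block size will not be disclosed to the investigators, and both the investigators and the patients will be blinded to group allocation".

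**Setting and size (2.2 Study Design; 4.10.1 Sample Size Calculation).** There is one clinic: "One hundred twenty patients from the outpatient clinic at the Gastroenterology Department of the Medical University of Lodz (Poland) will be enrolled". On numbers, "the sample size was ultimately set to 60 participants/cases per group, with a total of 120 patients to be included in the study". No stratification is mentioned, so a single list is assumed below.

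**Dispensing (2.2).** "The study products will be provided to participants at the baseline visit and at the week 4 visit". Each patient therefore has to be matched to the assigned product twice.

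**The concern.** A code with one value per arm ties all patients in an arm together. With a number per participant, breaking the blind for one person reveals one assignment. With A/B it reveals the meaning of both letters, and so the treatment of everyone whose letter is known.

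The fixed block of 4 adds a second weakness. If the letters can be followed in order, the list becomes partly predictable, because a block in which one letter is used up can only continue with the other. The article protects this by keeping the block size from the investigators, but it prints the block size in the same section.

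Blinding and concealment matter a great deal in this trial. All four primary instruments (IBS-SSS, IBS-GIS, IBS-AR, IBS-QOL) are patient-reported, and participants are telephoned weekly. Some entry criteria in 3.1 rest on the investigator's judgement, for example general condition and the clinical significance of laboratory results. Some discontinuations under 3.3 are made by the investigator after allocation. Section 5 names the double-blind design among the main strengths. If blinding or concealment is lost, the analysis cannot restore it.

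**Working it through.** **Inputs.** Two letters, two products, two arms (2.4); fixed block size 4 (2.3); 120 patients, 60 per group (4.10.1); one clinic (2.2). Assumptions: each letter stands for one arm, which is the plain reading of 2.4; one unstratified list.

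**1. The plan's own figure.** 120 / 4 = 30 blocks; 30 × 2 = 60 per arm. This matches 4.10.1. The article gives no figure for predictability.

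**2. Letters that are certain in advance.** There are 6 equally likely blocks of 4. A position is certain when one letter is already used up:

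| Block | Certain positions |
|---|---|
| AABB | 2 |
| BBAA | 2 |
| ABAB | 1 |
| ABBA | 1 |
| BAAB | 1 |
| BABA | 1 |
| Total | 8 of 24 |

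8/24 = 1/3; 120 × 1/3 = 40 patients expected.

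**3. Best-guess accuracy.** Guess the letter with more remaining, or toss a coin if equal.
- Position 1: 1/2.
- Position 2: 2/3.
- Position 3: balanced so far with probability 2/3 (accuracy 1/2), otherwise certain: 2/3 × 1/2 + 1/3 × 1 = 2/3.
- Position 4: 1.

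Mean = (1/2 + 2/3 + 2/3 + 1)/4 = 17/24 = 70.8%, against 50% by chance. Simulating 400 lists of 120 patients gave 33.4% certain and 70.8% correct.

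**4. Can the block size be inferred from the letters?** Under simple randomization a given set of four is balanced with probability 6/16. Balance after every fourth patient for k sets has probability (6/16)^k: 37.5%, 14.1%, 5.3%, 2.0% and 0.7% for k = 1 to 5. By about 20 patients the pattern would stand out to someone who has all the letters. If certainty started only then, the expected number of certain letters would be (120 − 20)/3 ≈ 33 rather than 40.

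**5. Effect of one decoded patient.**
- A/B marking: both letters are decoded, exposing up to 120 of 120 assignments (all those whose letter is known). Block size plays no part.
- Participant-specific numbers: 1 of 120.

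**6. What each remedy changes.** The mixed-block rows are simulated, assuming equal chances for the listed sizes and an observer who knows the set of sizes.

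| Scheme | Certain from labels | Best guess | Exposed by one code break |
|---|---|---|---|
| A/B, fixed 4 | 33.3% | 70.8% | up to 120 |
| A/B, mixed 4/6 | about 5% | about 69% | up to 120 |
| A/B, mixed 4/6/8 | about 2% | about 68% | up to 120 |
| Participant-specific numbers | 0 | 50% | 1 |

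The label is the larger problem; the block size is secondary.

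**The case against.** The strongest reply has five parts.

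**The article does not say that A or B is the sole identifier.** A reader might infer that no patient or kit number exists. The text does not support that, and a condensed article may omit one. This stands. An extra number would not cancel the stated A/B mark, however.

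**Staff may not see the letter.** Section 2.4 puts the mark on the capsules and describes the packs as alike, with no letter in the inscription. Someone handing over a closed pack may see nothing, and who dispenses is not stated. This stands, and it is why the prediction figures are upper bounds. Patients who open the pack would still see their own letter.

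**What can be predicted is a letter, not a treatment.** A reader might conclude that staff can predict a third of treatment allocations. The documents do not support this. The observer needs the earlier letters in order, the block size and the block start, and the letter must also be decoded or guessed. In addition, eligibility is judged at screening, up to two weeks before randomization, when a patient's place on the list may be unknown.

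**The block size is withheld.** Section 2.3 says so, and nothing shows when the published figure became available relative to recruitment. That weakens the prediction argument for early patients. It does nothing about group-level unblinding.

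**A code break is hypothetical.** The article describes none. Section 3.3 discontinues a patient after a serious adverse event but does not call for unblinding, and 4.9 calls the study minimal-risk. This is fair as to likelihood. It does not change the consequence if one patient's treatment becomes known.

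**Conclusion.** The point holds in a conditional form. Marking product with one letter per arm is a stated design feature, not a detail left out of an article. Its consequence follows directly: learning one patient's treatment decodes both arms for every patient whose letter is known, up to 120 of 120. Withholding the block size has no bearing on this.

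The fixed block of 4 adds predictability of the next letter: at most an expected one third with certainty (40 of 120) and about 71% by best guess. Both figures assume sight of all earlier letters in order and a known or inferred block size and block start. They become predictions of treatment only after a letter is decoded or guessed.

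The documents do not show that concealment or blinding has failed, nor how many staff can see the letters. No size can be given for any resulting bias in the patient-reported outcomes. The point rests on the plain reading that A and B each denote one arm.

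**What to change.** **Main change.** Replace the A/B mark, on the capsules and on the packs if it also appears there, with participant-specific kit numbers that cover both the baseline and the week 4 supply. Have the kit-to-arm list held only by the supplier or an independent statistician, and make any code break per kit. Amend 2.4 accordingly. If the letter is on the capsule itself, remaining stock must be re-marked; over-labelling the pack would leave the letter visible.

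**Supplementary change.** Use randomly varying block sizes and do not publish them. This lowers certain predictions from 33% to about 2–5%. On its own it leaves best guessing at about 68–69% and does not solve the two-letter problem.

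**If enrolment has started.** Apply both changes to the remaining patients under a new list. If the full protocol already uses participant-specific numbers, 2.4 should say so and state whether the A/B mark is still visible on what is dispensed.

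**Cost.** A new randomization list and new labels from the supplier, plus re-marking of stock where the capsule carries the letter. No extra patients or visits.

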## 3. Patients

The study will include 120 adult patients with IBS. IBS will be diagnosed according to Rome IV criteria, i.e., recurrent abdominal pain (felt in the last three months at least one day a week on average), associated with two or more of the following criteria: (1) related to defecation, (2) associated with a change in stool frequency, (3) associated with a change in the form (appearance) of stool [30]. Stool consistency (without the use of any antidiarrheal or laxative agents) will be assessed with the Bristol Stool Form (BSF) scale [31].

### 3.1. Inclusion Criteria

Patients with any of the following forms of IBS will be included:IBS-D—more than 25% of BSF type 6 and 7 stools, and less than 25% of type 1 and 2 stools;IBS-C—more than 25% of BSF type 1 and 2 stools, with less than 25% of type 6 and 7 stools;IBS-M—more than 25% of BSF type 6 and 7 stools and also more than 25% of type 1 and 2 stools.

To be eligible for the trial, subjects must meet all of the inclusion criteria and none of the exclusion criteria, as stated below.

The following inclusion criteria will be used:males and females aged from 18 to 70 years, inclusive;a good physical and mental condition assessed based on the patient’s history and physical examination;laboratory test results (complete blood count, blood chemistry panel) within normal limits or considered not to be clinically significant by the investigator;a voluntarily provided written informed consent;IBS with at least moderate symptom severity, defined as an IBS-Severity Scoring System (IBS-SSS) score of >175 points [32];the ability to strictly adhere to the investigators’ instructions regarding study procedures and protocol requirements.

### 3.2. Exclusion Criteria

Exclusion criteria will include:unclassified IBS;gastrointestinal conditions other than IBS, including clinical or endoscopic diagnosis of gastroenteritis, celiac disease, or inflammatory bowel disease;other diseases, such as respiratory disorders (asthma, chronic obstructive pulmonary disease); cardiovascular disorders, including uncontrolled hypertension (blood pressure > 170/100 mmHg); endocrine disorders, including diabetes mellitus (fasting blood glucose > 11 mmol/L) or thyroid diseases; severe neurological conditions, including psychosis; malignancy; and hepatic or renal impairment;unexplained blood biochemistry abnormalities: serum creatinine levels over twice the upper limit of normal, AST or ALT levels over twice the upper limit of normal;pregnancy or breastfeeding;hypersensitivity to soy or other food allergens;lactose intolerance;a surgical procedure scheduled during the course of the clinical study;the use of gastrointestinal motility stimulants or dietary fiber supplements during the two weeks preceding the clinical study;the use of antithrombotic drugs;current use of gut microbiota-targeted dietary supplements or drugs, such as probiotics, prebiotics, synbiotics, SCFAs, and a refusal to undergo a 1-month washout period;antibiotic therapy during the one month preceding the study;antibiotic use during the study;any drugs, except contraceptive pills or intramuscular contraceptives, hormone replacement therapy (estrogen/progesterone), L-thyroxine, antidepressants at low doses (up to 25 mg of amitriptyline, nortriptyline, or a selective serotonin reuptake inhibitor per day), antihypertensive drugs at low doses (diuretics, angiotensin-converting enzyme inhibitors, angiotensin receptor antagonists) and provided they have been used at a stable dose and for at least one month prior to the study;being included in another clinical study during the previous three months;a history of alcohol or substance abuse;COVID-19 infection, contact with any COVID-19-positive individuals during the previous two weeks.

